# Efficacy of customized corneal crosslinking versus standard corneal crosslinking in patients with progressive keratoconus (C-CROSS study): study protocol for a randomized controlled trial

**DOI:** 10.1186/s12886-023-02976-4

**Published:** 2023-05-19

**Keywords:** Keratoconus, Crosslinking, Customized

## Abstract

**Background:**

Keratoconus is a degenerative disorder of the cornea leading to a protrusion and thinning with loss of visual acuity. The only treatment to halt the progression is corneal crosslinking (CXL), which uses riboflavin and UV-A light to stiffen the cornea. Recent ultra-structural examinations show that the disease is regional and does not affect the entire cornea. Treating only the affected zone with CXL could be as good as the standard CXL, that treats the entire cornea.

**Methods:**

We set up a multicentre non-inferiority randomized controlled clinical trial comparing standard CXL (sCXL) and customized CXL (cCXL). Patients between 16 and 45 years old with progressive keratoconus were included. Progression is based on one or more of the following changes within 12 months: 1 dioptre (D) increase in keratometry (Kmax, K1, K2); or 10% decrease of corneal thickness; or 1 D increase in myopia or refractive astigmatism, requiring corneal crosslinking.

**Discussion:**

The goal of this study is to evaluate whether the effectiveness of cCXL is non-inferior to sCXL in terms of flattening of the cornea and halting keratoconus progression. Treating only the affected zone could be beneficial for minimalizing the risk of damaging surrounding tissues and faster wound healing. Recent non-randomized studies suggest that a customized crosslinking protocol based on the tomography of the patient’s cornea may stop the progression of keratoconus and result in flattening of the cornea.

**Trial registration:**

This study was prospectively registered at ClinicalTrials.gov on August 31^st^, 2020, the identifier of the study is NCT04532788.

## Background

Keratoconus is a degenerative disorder of the cornea involving disruption and loss of the native collagen network leading to severe corneal thinning [1–3], which eventually results in a typical cone shaped cornea causing irregular astigmatism and impaired visual acuity [4]. Recent ultra-structural examinations show that the disease does not affect the entire cornea in its early stage, but rather starts locally [1, 5].

The onset of keratoconus is during puberty and gradually progresses until the mid-20 s and 30 s [4]. Around the age of 40 the disease stabilizes, showing hardly any progression in patients older than 45. With a prevalence of approximately 265 cases per 100,000 individuals and an incidence of approximately 13 cases per 100,000 in the Netherlands, the disorder is relatively common [6]. While the cause of keratoconus is not fully understood, disease progression seems to be influenced by genetic and environmental factors. An increased prevalence of the disease has been associated with systemic disorders e.g., atopy, Down syndrome, and Marfan syndrome [7].

The treatment for keratoconus depends on the severity of the disease [8]. In its initial stage, treatment aims at improving visual acuity. This can be achieved with glasses and specialized contact lenses but also by implanting intrastromal corneal ring segments to regularize the corneal shape. Although these treatments may improve visual acuity, they do not cure keratoconus.

Until two decades ago the only treatment for advanced keratoconus was corneal transplantation, an invasive technique with a chance of corneal graft rejection and the need of retreatment after a few years [9, 10]. In addition, corneal transplantation has an important impact on the quality of life and the outcome may be suboptimal because of significant post-keratoplasty astigmatism.

In 2003 Wollensak et al. introduced corneal crosslinking (CXL) to halt the progression of keratoconus in humans [11]. First the top layer of the cornea, the epithelium, is debrided after which the cornea is soaked for 30 min with the photosensitizer riboflavin. Hereafter a 9.0 mm diameter Ultraviolet-A (UV-A) beam radiates the cornea for 30 min with a fluence of 3 mW/cm^2^ resulting in a total energy of 5.4 J/cm^2^. This protocol is called the Dresden protocol. Currently, accelerated versions of the Dresden protocol are used in clinical practice with different fluences of 9mW/cm^2^, 10mW/cm^2^ and 15 mW/cm^2^. The higher the fluence, the shorter the treatment time, in which, according to the Bunsen–Roscoe reciprocity law, the total amount of energy stays the same [12–14]. During the corneal crosslinking oxygen radicals are formed that interact with the surrounding molecules, leading to the formation of new chemical bounds between the collagen fibrils (i.e. corneal crosslinks) [15], with the final goal to stiffen the cornea and halt the progression of the disease.

For any treatment, it is desirable that unaffected regions of the tissue involved are not unnecessarily treated by an intervention or drug application. To minimize the risk of damage to surrounding tissues in CXL it would be beneficial that the UVA beam is restricted only to the affected, keratoconic zone in the patient’s cornea [16]. This can be achieved by *customizing* the beam shape and size in a way that only the degenerated zone is treated, i.e., by customized crosslinking (*c*CXL). Recently, studies provided clinical evidence that similar clinical outcomes can be achieved if only the cone is treated rather than the whole cornea [17–20]. We hypothesized based on the results of these previous studies that only treating the affected zone has three potential benefits: (1) a faster recovery (e.g. increased corneal reepithelialisation), (2) stronger flattening of maximum keratometry and (3) better visual outcome (corrected distance visual acuity, CDVA). However, since none of these studies were randomized and study results were limited by small sample sizes, there is a need for a randomized controlled trial with an appropriate design and sample size to confirm these findings. This study will be setup as such, with the aim to investigate whether *c*CXL is non-inferior to *s*CXL in terms of halting the disease progression and flattening of the corneal surface.

## Methods

### Objectives

The primary objective is the change in maximum keratometry (Kmax) measured with a Scheimpflug-based tomographer (Pentacam® HR, OCULUS Optikgeraete GmbH, Wetzlar, Germany). Under the subheading ‘Outcome measures’ all the secondary objectives are summed up and explained.

### Study design

We will set up a multicentre non-inferiority randomized controlled clinical trial at Maastricht University Medical Centre + , University Medical Centre Utrecht and University Medical Centre Groningen.

### Study population

Patients will be included from the outpatient ophthalmology department at the three academic centres. Inclusion criteria are patients between the age of 16 and 45 years old with progressive keratoconus based on one or more of the following changes within 12 months: 1 dioptre (D) increase in keratometry (Kmax, K1, K2) or 10% decrease of corneal thickness or 1 D increase in myopia or refractive astigmatism. Exclusion criteria are corneal scarring, corneal diseases other than keratoconus, history of corneal surgery (e.g. refractive surgery, corneal transplantation, intracorneal ring segments), unwilling or unable to give informed consent, unwilling to accept randomization or inability to complete follow-up (e.g. hospital visits) or comply with study procedures, insufficient corneal thickness including epithelium < 400 µm, pregnancy, if both eyes are eligible only the first eye which is undergoing corneal crosslinking is enrolled in the study, or participation in another clinical study.

### Study procedures

#### Crosslinking procedures

Before the CXL procedure the treatment location of the customized procedure needs to be determined. A patient-specific treatment pattern, based on the patient’s Pentacam images, will be used to treat the cornea. The CXL treatment pattern exists out of three circles and is centred on the cone. To estimate the cone location a combination of the thinnest corneal point, maximum anterior elevation and maximum posterior elevation is used. The average of these three points is calculated and functions as the centre for the treatment pattern. The treatment pattern itself consists of three concentric circles. The diameter of the smallest circle is 4 mm, of the middle circle 5.2 mm and of the biggest circle is 6 mm. Each circle receives a different amount of energy, which gradually decreases with increasing circle size. The smallest circle receives the highest amount of energy, 10 J/cm^2^, this is equal to a fluence of 10 mW/cm^2^ for 16.7 min. The middle circle receives 7.2 J/cm^2^ and the biggest circles receives 5.4 J/cm^2^ (Fig. 1). The patient-specific treatment pattern will be marked on the cornea centred on the cone location.

**Fig. 1 Fig1:**
[figure not shown]
Customized treatment pattern

The first step of the CXL procedure is the removal of the epithelium. In the sCXL protocol, the epithelium is debrided with alcohol 20% over a region with a diameter of 9.0 mm. In the cCXL the cone location is marked and the epithelium is removed with alcohol 20% over a region with a diameter of 6.0 mm. After the removal of the epithelium the pachymetry is measured, if it is more than 400 µm, the cornea is soaked with 0.1% riboflavin, saline, HPMC (VibeX RapidTM) 1 drop every 2 min for 10 min. The pachymetry is measured a second time. If the pachymetry is less than 400 µm, hypotonic riboflavin is applied until the cornea is thicker than 400 µm. After the application of riboflavin, the cornea is irradiated with UV-A light. In sCXL a fluence of 10 mW/cm^2^ is used during 9 min with a diameter of 9.0 mm, this gives a total energy of 5.4 J/cm^2^. In cCXL the cornea is irradiated with UVA-light according to the treatment pattern mentioned earlier. Both procedures are done with the Avedro Mosaic CXL device (Avedro, Inc. Waltham, Massachusetts, United States).

#### Postoperative care

Postoperative topical medication is started at the day of surgery and is similar for both groups. Trafloxal (Ofloxacin (3 mg/ml), Bausch and Lomb) eye drops are prescribed 3 times daily for 1 week. Duratears (dextran 70 (1 mg/ml) and hyperomellose (3 mg/ml), Alcon) eye drops are prescribed 8 times daily. At the follow-up visit at day 4, the epithelial healing is evaluated. The bandage contact lens is removed if the epithelial defect is closed, and Trafloxal (Ofloxacin (3 mg/ml), Bausch and Lomb) is continued for another 3 days. One week after the CXL procedure FML Liquifilm (fluorometholon (1 mg/ml), Allergan) is started 2 times a day for 3 weeks. Duratears (dextran 70 (1 mg/ml) and hyperomellose (3 mg/ml), Alcon) is continued as needed.

#### Follow-up

A baseline measurement will take place during the preoperative visit for demographic variables, routine eye examinations, visual acuity, and corneal tomography. For both groups, these measurements will be repeated during postoperative visits. These follow-up study visits will be scheduled 4 days, 4 weeks, 3 months, 6 months, and 12 months after the crosslinking procedure. Additional visits will be planned if needed in case of complications. A more detailed overview of the study measurements per follow-up visit is presented in Table 1.

**Table 1 Tab1:** Study procedures per follow-up time point

Assessment/Procedure	Preoperative visit	Follow-up visits				
		4 days	1 month	3 months	6 months	12 months
Check for in-/exclusion criteria	X					
Informed consent	X					
Medical history/ Demographics	X					
Check medication	X	X	X	X	X	X
Visual acuity	X		X	X	X	X
Refraction	X					X
Slit lamp examination	X	X	X	X	X	X
Fundoscopy	X					
IOP	X		X			
ECD	X				X	X
Pentacam	X		X	X	X	X
Anterior segment OCT			X			
Questionnaires						
• NEI VFQ-25	X			X	X	X
• KORQ	X			X	X	X
• EQ-5D-5L	X			X	X	X
• HUI-3	X			X	X	X
• Standardized cost questionnaire	X			X	X	X
• SF-MPQ		X				

*IOP* Intraocular pressure (mmHg), *ECD* Endothelial cell density (cells/mm^2^)

#### Outcome measures

The primary outcome is the mean change in Kmax 12 months after CXL procedure measured with the Pentacam® HR (OCULUS Optikgeraete GmbH, Wetzlar, Germany).

We also set multiple secondary objectives:Visual acuity: uncorrected and corrected distance visual acuity (UDVA and CDVA) in LogMAR (the Logarithm of the Minimum Angle of Resolution)RefractionDepth and size of demarcation linePachymetry: change in thinnest corneal thicknessZonal Kmax: the analysis of a 3.0 mm zone centred on KmaxDUCK score: Dutch Crosslinking for Keratoconus Score is based on changes in 5 clinical parameters that are routinely assessed: age, visual acuity, refraction error, keratometry, and subjective patient experience. Each item is scored from 0 to 2 and cut-offs are determined by clinical experience [21].ABCD grading system: the Anterior radius of curvature (A), Posterior radius of curvature (B), Corneal pachymetry at thinnest point (C), Distance best corrected vision (D), and a modifier ( −) for no scarring, ( +) for scarring that does not obscure iris details and (+ +) for scarring that obscure iris details measured with the Pentacam HR [22].Success/failure rate: failure is defined as progression of the disease after CXLMean endothelial cell lossRate of reepithelialisation: evaluated at 4 days after CXL with fluorescein and blue light, a slit lamp image is taking to perform quantitative morphometric surface analysisPatient Reported Outcomes Measures (PROMs):∘ Vision specific quality of life and patient satisfaction will be measured using the National Eye Institute Visual Function Questionnaire-25 (NEI-VFQ-25) and the Keratoconus Outcome Research Questionnaire (KORQ)∘ Health-related quality of life (HRQL) will be measured using two questionnaires: EuroQol’s EQ-5D-5L and the Health Utilities Index Mark-3 (HUI-3)∘ Pain after CXL will be measured with the short form of the McGill Pain Questionnaire (SF-MPQ) during the first 4 days after CXLIncremental cost-effectiveness ratios (ICERs): These will be expressed as∘ incremental societal costs per quality-adjusted life year (QALY) gained based on the EQ-5D and HUI-3∘ incremental healthcare costs per patient with a reduction in Kmax of ≥ 1D after CXL, per clinically improved patient on the NEI VFQ-25 questionnaire, per clinically improved patient on the Keratoconus Outcome Research Questionnaire, and with clinical improvement in (un-) corrected distance visual acuityBudget impact: will be reported as the difference in costs resulting from implementation of cCXL, from the perspective of the budget holder. Different scenario’s will be compared to investigate the impact of various levels of implementation (i.e., 25%, 50%, 75% and 100% of eligible patients).

#### Adverse events

Adverse events are defined as any undesirable experience occurring to a subject ‘s eyes during the study, whether considered related to the trial procedure or the experimental intervention. All adverse events reported spontaneously by the subject or observed by the investigator, or his staff will be recorded, unless the event is of negligible impact and in addition has no connection to the study anywise.

The investigator will report all serious adverse events (SAE) to the sponsor without undue delay after obtaining knowledge of the events, except for the SAE’s unrelated to the intervention [23, 24]. The sponsor will report the SAEs through the web portal ToetsingOnline to the accredited medical ethical commission that approved the protocol, within 7 days of first knowledge for SAEs that result in death or are life threatening followed by a period of maximum of 8 days to complete the initial preliminary report. All other SAEs will be reported within a period of maximum 15 days after the sponsor has first knowledge of the serious adverse events.

### Statistical analysis

An electronic data capture program (Castor EDC) will be used to collect all data. Data analysis will be done with SPSS (SPSS Inc. Chicago, IL). Data analysis will be performed according to the intention-to-treat principle. Patients who reach a safety end point (e.g., additional intervention) and those lost to follow-up will still be included in the analysis. Per-protocol analysis will be performed as an addition to the intention-to-treat principle. Non-inferiority will be established if both analyses yield the same result.

Descriptive statistics will be used to present the baseline characteristics and a CONSORT diagram will describe the course of patients through the trial, details of the number of eligible patients, the number of informed consents and the number of randomized patients.

For the primary outcome, (the change from baseline in) Kmax, a linear mixed model analysis will be used, since it accounts for baseline differences, uses all available data, and corrects for correlation between repeated measures. Next to Group (cCXL vs. sCXL), Time and Interaction Group*Time, the stratification variable (Kmax) as well as variables related to the outcome and/or to missingness of outcome variable will be included in the fixed part of the model. For the secondary outcomes that are repeatedly measured, we will use the same model as for the primary outcome namely a linear mixed model to assess for overall differences between groups over time (quantitative, continuous data).

A trial-based economic evaluation will be performed within a time horizon of 12 months to estimate the cost-effectiveness (CEA) of cCXL compared to sCXL. Both a societal and healthcare perspective will be used. Incremental cost-effectiveness ratios (ICERs) will be calculated by dividing the difference in costs by the difference in effectiveness between cCXL and sCXL. A micro-costing method will be used to determine the costs in the study population. A detailed and complete analysis of the costs of each patient will be included in the study up to 12 months. The primary effectiveness measure used in the base case cost-effectiveness analysis is QALY. QALYs will be calculated based on generic HRQL, using two questionnaires: EuroQol’s EQ-5D-DL (base case analysis) and the HUI-3.

The budget impact analysis (BIA) will be performed to evaluate the impact of implementation of cCXL on the Dutch healthcare budget, compared to sCXL. The BIA will be performed in accordance with the Dutch guidelines for economic evaluations and the ISPOR guidelines (the Professional Society for Health Economics and Outcomes Research) [25, 26].

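### Kmax measured after an additional intervention appears to count towards the assigned arm, which leans towards non-inferiority, and the undefined per-protocol set does not reliably correct it

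*Protocol article*

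**What the plan says.** All analysis statements below are in the Statistical analysis section of the protocol article.

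- Analysis set: "Data analysis will be performed according to the intention-to-treat principle".
- Patients with an additional intervention: "Patients who reach a safety end point (e.g., additional intervention) and those lost to follow-up will still be included in the analysis".
- Primary model: "a linear mixed model analysis will be used, since it accounts for baseline differences, uses all available data, and corrects for correlation between repeated measures". The fixed part holds group, time, their interaction, the Kmax stratum, and variables related to the outcome or to missingness. No term or rule for an additional intervention is named.
- Second set and decision rule: "Per-protocol analysis will be performed as an addition to the intention-to-treat principle", and "Non-inferiority will be established if both analyses yield the same result". The per-protocol set is not defined.

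Under Outcome measures, "The primary outcome is the mean change in Kmax 12 months after CXL procedure". Progression after CXL is a failure there, but only as a secondary outcome. Table 1 schedules Pentacam scans at 1, 3, 6 and 12 months, so progression can be seen before the endpoint. Nowhere does the article say when an additional intervention is given, how often it is expected, or what it does to Kmax.

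**The concern.** The trial asks whether treating only the cone halts progression and flattens the cornea as well as treating the full zone. An eye that progresses after its randomised procedure is a failure. If it then has an intervention that lowers Kmax, and the later Kmax enters the model, that failure adds a flattened cornea to its arm's mean. If this happens more often under cCXL, the observed deficit is smaller than the true one. In a non-inferiority trial that is the anti-conservative direction.

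The usual safeguard is a per-protocol analysis that must agree. It fails here in either form:

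- If the set excludes retreated eyes, it removes the failures themselves.
- If it keeps them with their later Kmax, it repeats the intention-to-treat bias.

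At stake is a claim of non-inferiority that partly reflects the second intervention rather than the first.

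**Working it through.** The plan gives no figure for this effect, so there is none to reproduce. The check asks how far the rule could move the primary comparison.

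**Inputs from the protocol article.** Sample size calculation: margin 0.3 D, SD 1.72 D, one-sided alpha 0.025, 55 analysed per group, planned mean change of -1.0 D. Study population: "1 dioptre (D) increase in keratometry (Kmax, K1, K2" as one criterion of progression at entry.

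**Assumptions.** Changes are normal, the sCXL mean is -1.0 D, and the true cCXL deficit equals the margin (cCXL mean -0.70 D). A single 12-month comparison stands in for the mixed model. Every eye that would worsen by 1 D or more is retreated in time for the effect to show at month 12. The gain per retreated eye is 1 D, or 2 D, or a reset to -1.0 D. The 1 D trigger is borrowed from the entry criterion and is not a stated retreatment rule.

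**Step 1, general relation.** Hidden deficit = (difference in retreatment rate) x (Kmax gain per retreated eye). With SE = 1.72 x sqrt(2/55) = 0.328 D, the intention-to-treat false non-inferiority rate at a true 0.30 D deficit is Phi(hidden/SE - 1.96):

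- 5 points x 1 D = 0.05 D hidden: 3.5%
- 10 points x 2 D = 0.20 D hidden: 8.8%
- 15 points x 2 D, or 30 points x 1 D = 0.30 D hidden (full erasure): 14.8%

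**Step 2, same trigger in both arms.** Share retreated:

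- cCXL: 1 - Phi((1 + 0.70)/1.72) = 16.1%
- sCXL: 1 - Phi((1 + 1.00)/1.72) = 12.2%

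The gap is 3.9 points, so a gain of 1 D hides 0.039 D and a gain of 2 D hides 0.078 D.

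For the reset case, the means of the eyes not retreated (truncated normal) are -1.202 D and -1.398 D. The arm means become 0.839 x (-1.202) + 0.161 x (-1.0) = -1.169 D and 0.878 x (-1.398) + 0.122 x (-1.0) = -1.349 D. The difference is 0.180 D, so 0.120 D is hidden.

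A per-protocol set without retreated eyes shows -1.202 - (-1.398) = 0.196 D.

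**Step 3, false non-inferiority rates** (simulation, 40,000 runs, 55 per arm; per-protocol set excludes retreated eyes):

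| Effect of retreatment | Apparent deficit, ITT | ITT alone | Both required |
|---|---|---|---|
| gain 1 D | 0.26 D | 3.7% | 2.4% |
| gain 2 D | 0.22 D | 4.9% | 3.6% |
| reset to -1.0 D | 0.18 D | 7.3% | 5.6% |

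Per-protocol alone gives about 5.7%. With no retreatment the same simulation gives about 2.6%, so the first row shows no inflation under the two-analysis rule. Repeat runs place the top figure between 5.5% and 5.7%. If the per-protocol set instead kept retreated eyes with their later Kmax, it would add no protection on this point and the ITT column would apply.

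**Dependence on sample size.** The 55 per group is taken as given. It does not follow from the stated inputs with equal true means: 2 x 1.72^2 x (1.960 + 1.282)^2 / 0.3^2 gives 691. That is a separate matter, but a fixed shift weighs more as the SE falls. At 691 per group the two-analysis rates are about 6% to 26%.

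**The case against.** The strongest reply is that the sentence speaks of patients, not measurements. A mixed model can keep a patient on pre-intervention values alone, so the text is compatible with setting later Kmax aside. A journal article also leaves much detail to the full protocol. This stands in part: a reader might infer that the plan deliberately uses post-intervention Kmax with no adjustment, and it does not say so. What remains is that the article foresees the event, fixes that the patient stays in, and pairs this with a model on all available data. Using the later values is the natural reading, and nothing corrects it.

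Second, additional intervention is labelled a safety end point, progression is handled separately as failure, and no link from progression to retreatment is stated. That is correct, so the size must remain conditional.

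Third, a reader might infer that a real deficit would be erased. Suppose 20% of cCXL and 5% of sCXL eyes go to +1 D and the rest reach -1.0 D. The means before retreatment are 0.80 x (-1) + 0.20 x 1 = -0.60 D and 0.95 x (-1) + 0.05 x 1 = -0.90 D. Retreating all failures to -1.0 D makes the 0.30 D gap vanish. The protocol does not support these inputs. It gives no rates, -1.0 D is the planned average of the whole intervention group rather than of successful eyes, and +1 D is an entry criterion. Progression, detection, retreatment and full response would also have to fit within 12 months.

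Fourth, excluding prior corneal surgery at entry ("history of corneal surgery (e.g. refractive surgery, corneal transplantation, intracorneal ring segments") does not contradict keeping patients who have surgery after randomisation. This stands, and the point does not rely on it.

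Finally, carrying forward the last pre-intervention Kmax is a single imputation, possibly from an early visit. As the sole primary method it would be contestable.

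**Conclusion.** The point holds as a moderate bias in the anti-conservative direction. It is not a demonstrated false result. On the natural reading, Kmax after an additional intervention is credited to the assigned arm, and the requirement that two analyses agree limits the bias without reliably removing it.

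Under the assumed 1 D trigger in both arms, the hidden amount is 13% to 40% of the margin (0.039/0.30 to 0.120/0.30). The false non-inferiority rate under the two-analysis rule runs from no inflation to roughly double the nominal level. These figures rest on the assumed trigger, gains, normality and timely retreatment, and on a per-protocol set that excludes retreated eyes. If few eyes are retreated within 12 months, or retreatment is balanced, the effect is negligible. Worth fixing before data are seen, but not a ground for rejecting the design.

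**What to change.** 1. Keep all randomised patients and the intention-to-treat analysis.
2. Pre-specify a second analysis of the primary outcome that does not credit the additional intervention to the assigned arm. For example, set aside Kmax measured after an additional corneal intervention on the study eye, and replace it by the last pre-intervention value or by an imputation that treats the eye as a failure. Require the non-inferiority conclusion to be consistent with this analysis.
3. State that no patient leaves the per-protocol set because of an additional intervention given for progression. This does not suffice without item 2, since the set would then carry the same post-intervention Kmax.
4. Count such an intervention as a failure in the success/failure outcome.
5. Record the date and type of any additional intervention in the CRF.

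The cost is some analysis wording, one further model run and one CRF item. No extra measurement is needed, because the scheduled Pentacam scans supply the pre-intervention value. The downside is a slightly less favourable cCXL estimate if retreatments are unbalanced, and one more analysis with which the conclusion must agree. Nothing here changes when or how patients are treated.

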### Sample size calculation

For non-inferiority, we assume that the intervention group should have an average decrease in Kmax of 1.0 D, based on clinical experience and recent evidence. The non-inferiority margin is equal to -0.3 D (i.e., the mean difference between cCXL and sCXL should be greater than -0.3 to achieve statistical significance). Assuming this non-inferiority margin and a within-group standard deviation (SD) of 1.72 D, we need to include 55 patients per group to detect non-inferiority with 90% power and a one-sided significance level alpha of 0.025. The sample size was calculated using an online calculator for the comparison of two means (www.powerandsamplesize.com). Accounting for 10% loss-to-follow-up, we need to include 62 patients per group, i.e., 124 patients in total.

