### Randomisation and blinding

Participants of the study will be randomized to either cCXL or sCXL (control), after applying the stratification factor of ‘Kmax < 58D’ or ‘Kmax ≥ 58D’. Each patient will receive a randomization number from a computerized random number generator. In Castor EDC, the subject number will be linked to one of the treatment arms (either cCXL or sCXL) through block randomization. Random varying block sizes of 2 and 4 will be used. The randomization procedure will be done by the principal investigator.

Since it is clear to both patients and surgeons which intervention will be performed, blinding will not be possible. The investigator that performs postoperative examinations will be blinded. Potential deblinding will be logged in the case report form (CRF).

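### The primary mixed model names baseline Kmax only as the 58 D stratification factor, leaves the response open, and admits unnamed, outcome-dependent covariates not limited to pre-randomisation variables

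*Protocol article*

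**What the plan says.** The endpoint is clear. Under Outcome measures: "The primary outcome is the mean change in Kmax 12 months after CXL procedure". The model is less so. Statistical analysis describes the response with an optional bracket: "the change from baseline in) Kmax, a linear mixed model analysis will be used, since it accounts for baseline differences". Both Kmax itself and its change fit that wording.

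The fixed part holds group, time and their interaction. Beyond those, "the stratification variable (Kmax) as well as variables related to the outcome and/or to missingness of outcome variable will be included". The stratification variable is defined once, under Randomisation and blinding, as two levels: "after applying the stratification factor of ‘Kmax < 58D’ or ‘Kmax ≥ 58D". No other covariate is named, no selection procedure is given, and nothing confines the covariates to measurements taken before randomisation. The same section applies this model to the repeatedly measured secondary outcomes.

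Study design describes three centres ("We will set up a multicentre non-inferiority randomized controlled clinical trial"). Centre is neither a stratification factor nor a named covariate.

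**The concern.** Two things are at stake, and they differ in kind.

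The first is precision. Baseline Kmax is measured on a continuous scale in every patient, and is likely to be related to the later change. If it enters only as below or above 58 D, part of what it explains stays in the residual, and the interval compared with a 0.3 D margin is wider than it need be. The statement that the model accounts for baseline differences would then be only coarsely true.

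The second is what the model estimates. Covariates that enter because they relate to the outcome, or to its missingness, can be identified only from outcome data. Measurements made after treatment can meet the rule. The trial collects day-4 re-epithelialisation, demarcation-line depth and size, and change in thinnest pachymetry. The arms differ by design in debrided diameter (9.0 against 6.0 mm) and in energy (5.4 against up to 10 J/cm²), so these measurements may respond to allocation. Conditioning on such a variable means the group coefficient is no longer the total treatment effect.

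**Working it through.** The article gives no figure for covariate adjustment, so there is none to reproduce. From Sample size calculation I take the SD (1.72 D), the margin ("The non-inferiority margin is equal to -0.3 D"), the one-sided 0.025 level and 55 analysed per group (110 in all). The 55 serves only as the planned number; how it was derived does not bear on this point. The share of patients above 58 D, the correlation r between baseline Kmax and its change, and all mediator inputs are assumptions.

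**1. Does the choice of response settle the baseline question?** No.
- If the response is change, subtracting baseline fixes its coefficient at 1 and leaves any correlation between baseline and change in place.
- If the response is Kmax with baseline as the first time level, and group and group*time are unconstrained, the 12-month contrast with complete data is (mean at 12 months − mean at baseline) in cCXL minus the same in sCXL. That is again a difference in change scores.

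On either reading, continuous baseline Kmax as a covariate adds something.

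**2. Information lost by the split.** For a normal baseline with proportion p above the cut c, the share of explained variance kept is f = φ(c)² / [p(1 − p)].
- p = 0.5: 0.3989² / 0.25 = 0.637
- p = 0.3: 0.3477² / 0.21 = 0.576
- p = 0.2: 0.2800² / 0.16 = 0.490

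The residual variance with the continuous covariate, relative to the split, is (1 − r²) / (1 − f·r²). The equivalent number of extra patients is 110/ratio − 110.

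| p above 58 D | r | ratio | reduction | extra patients |
|---|---|---|---|---|
| 0.5 | 0.3 | 0.91/0.9427 = 0.965 | 3.5% | 4 |
| 0.3 | 0.3 | 0.91/0.9482 = 0.960 | 4.0% | 5 |
| 0.2 | 0.3 | 0.91/0.9559 = 0.952 | 4.8% | 6 |
| 0.5 | 0.5 | 0.75/0.8408 = 0.892 | 10.8% | 13 |
| 0.3 | 0.5 | 0.75/0.8560 = 0.876 | 12.4% | 16 |
| 0.2 | 0.5 | 0.75/0.8775 = 0.855 | 14.5% | 19 |

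As 95% half-widths, 1.96 × residual SD × √(2/55), the unadjusted value is 0.643 D. At p = 0.2 and r = 0.5 it is 0.602 D with the split and 0.557 D with continuous Kmax. At p = 0.5 and r = 0.3 it is 0.624 D and 0.613 D.

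**3. Adjusting for a treatment consequence (illustration).** Orient the difference so that negative means less flattening with cCXL. Put the truth at the margin, −0.3 D, and let half of it run through a post-treatment variable whose within-arm correlation with the outcome is r_M. The adjusted estimate then centres on 0.5 × (−0.3) = −0.15 D, with standard error 1.72 × √(1 − r_M²) × √(2/55).
- Unadjusted: false non-inferiority = 1 − Φ(1.96) = 2.5%.
- r_M = 0.5: standard error 0.284; 1 − Φ(1.96 − 0.15/0.284) = 7.6%; simulation (10,000 runs) 7.4%.
- r_M = 0.8: standard error 0.197; 1 − Φ(1.96 − 0.15/0.197) = 11.5%; simulation 11.2%.

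If a quarter of the deficit is mediated, the simulated rates are 4.4% and 5.4%; if all of it is, 17.5% and 31.5%. The sign depends on the truth. If cCXL were better by 0.3 D and half of that were mediated, the same adjustment would shrink the estimate from +0.30 to +0.15 D, which works against cCXL.

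**The case against.** The strongest reply is that the article nowhere says post-treatment variables will be used; the candidates above are listed there as secondary outcomes. Covariate lists are usual analysis-plan content, and including predictors of missingness in a likelihood-based mixed model is a recognised way to support a missing-at-random assumption. The bracketed Kmax could mean the continuous value, and continuous Kmax would also qualify under the open clause. Adjusting for the stratification factor matches the randomisation, and a coarser covariate leaves the estimate unbiased and the interval merely wider, which is conservative for non-inferiority.

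Much of this stands. It would be too strong to say that baseline Kmax can enter only as a dichotomy: the form is ambiguous. It would also be too strong to call the absence of centre an error, since randomisation is not stratified by centre, nothing is contradicted, and centre could be specified elsewhere.

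Two things remain. The only definition given for the named variable is binary, so the efficient form is not secured. And the article does more than leave a list for later: it states a rule for what will enter the confirmatory model, and that rule depends on outcome data. Missingness predictors are harmless as fixed effects when measured before randomisation; when measured afterwards, they can change the estimand.

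**Conclusion.** The point holds as a specification weakness in the primary analysis that should be corrected. The precision loss is small to moderate: 3.5% to 14.5% of residual variance, or 4 to 19 patients in 110, given a normal baseline, a linear relation, r between 0.3 and 0.5, and 20% to 50% of patients above 58 D. The covariate rule matters more in principle, because it leaves the confirmatory estimate open to choices made after outcomes are known. The rise in false non-inferiority to about 7-11% rests wholly on assumed mediation and shows what the wording permits, not what is planned.

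Two stronger readings are not supported. A reader might infer that the bias always favours non-inferiority. It does so only if the variable carries part of a true cCXL deficit, and the article's own hypotheses of faster recovery and stronger flattening would make it run the other way. A reader might also infer that halving a 0.5 D deficit to 0.25 D would bring it inside the margin and so pass the test. The test uses the confidence bound: with a half-width of 0.643 D, an estimate of −0.25 D has a lower bound of −0.25 − 0.643 = −0.89 D, and non-inferiority would not be declared.

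**What to change.** State the primary model in full:
- Response: change from baseline in Kmax at each post-treatment Pentacam visit, with the 12-month group contrast as the primary estimate.
- Fixed part: group, visit, group*visit, continuous baseline Kmax, baseline Kmax*visit, and the 58 D stratum.
- Further covariates: only pre-randomisation variables, listed by name before any allocation-linked outcome data are seen. Centre may be added as one of these, as an option.
- Post-baseline predictors of missingness: only outside the treatment-effect model, for example as auxiliary variables in imputation.

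Carry the same rule over to the repeatedly measured secondary outcomes, each with its own baseline value where there is one.

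The cost is wording and a few degrees of freedom. With four post-treatment Pentacam visits in Table 1, baseline Kmax and its interaction with visit take 1 + 3 = 4, and three centres would take 2 more. No new data are needed.
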